**Fig. 1 Fig1:**
[figure not shown]
Study flowchart

### Sample size and power calculations

Power calculations and Internet dropout rates (30 %) [51, 52] were taken into consideration to estimate the necessary sample size to detect a large effect size (*d* = 1) with a power of 0.80 and an alpha of 0.05, based on a similar study [32] and recent systematic reviews [36]. The RCT will recruit a minimum of 57 participants, who will be randomly allocated to one of 3 experimental conditions.

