On the other hand, this type of computer-assisted treatment can be delivered through the Internet, which would improve the advantages of this way of applying exposure, reaching more people in need. The Internet has been shown to be an effective tool for treating a broad range of psychological disorders and psychiatric conditions, particularly depression and anxiety disorders [33–35], and it can address common treatment barriers such as limited access to mental health treatments [35]. Specifically, authors have pointed out five main advantages: efficacy, effectiveness, safety, geographical reach, acceptability, and convenience [36]. However, according to Andersson [33], in spite of the fact that specific phobias are common, only two studies with self-help Internet-based programs have been published, one on spider phobia [37] and one on snake phobia [38].

However, despite the proven efficacy of these programs, there are still some questions that remain unclear, such as the impact of clinician guidance. To date, evidence shows that guidance is a beneficial feature that leads to better adherence and better outcomes in programs administered through the Internet [34, 39–41]. Nevertheless, other authors have shown that unguided self-help interventions are useful alternatives with similar outcomes that might work using automated reinforcement [40, 42, 43]. Moreover, the results so far indicate a small but significant effect size of these self-help interventions compared to a control condition [43–47]. Therefore, more research is needed to examine and determine critical key aspects of clinician guidance that promote positive effects [36].

In sum, the Internet is a useful and effective tool for providing psychological treatments, and there is a large body of research about this topic. However, no published study has explored these issues in the research on FP. As far as we know, no controlled FP study has been published to test the efficacy of an Internet-based treatment.

The purpose of the randomized control trial (RCT) described in this study protocol is to investigate the effectiveness of an Internet-based exposure treatment for FP (*NO-FEAR Airlines*) versus a waiting list control group. Secondary objectives are: a) to explore two ways of delivering *NO-FEAR Airlines*, with or without therapist guidance, and b) to study the patients’ acceptance through expectations, preferences, and satisfaction with the online program. This paper presents the study design.

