Finally, there are several limitations that should be mentioned. First, the measurements (i.e., diagnostic interview and questionnaires) will be conducted online and via phone calls. Although some studies have shown the utility of online assessment and its concordance with traditional assessment [74–76], some evidence suggests that psychometric properties may change when assessment is conducted via the web [77]. Second, dropout rates are expected to be high (around 30 %), according to the literature [51, 52]. For this reason, dropout rates have been taken into account in the sample size calculation. Third, due to the heterogeneity of FP, the presence of comorbid disorders such as panic, agoraphobia, claustrophobia, and acrophobia may influence the study outcome measures. Although participants with comorbid disorders will not be excluded if FP is the primary diagnosis, this fact will be taken into account in the data analysis.

In summary, the results will contribute to the growing research on Internet-delivered treatments and the treatment of FP. *NO-FEAR Airlines* is intended to be an effective and useful tool to help people who may need it. This program has been designed to enhance the adherence, acceptance, and access to exposure-based treatments for FP. Finally, results from this study could help to improve the *exposure* technique application.

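### The 80% power stated for 57 participants is reached only by comparisons the plan does not name; each arm against waiting list has about 70%

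*Protocol article*

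**What the plan says.** The section Sample size and power calculations gives the inputs together. On dropout it says: "Power calculations and Internet dropout rates (30 %) [51, 52] were taken into consideration to estimate the necessary sample size". The target is "to detect a large effect size (*d* = 1) with a power of 0.80 and an alpha of 0.05". The result is: "The RCT will recruit a minimum of 57 participants, who will be randomly allocated to one of 3 experimental conditions". The limitations part of the Discussion returns to the 30% loss and adds: "For this reason, dropout rates have been taken into account in the sample size calculation". So 57 is the number randomised, with loss already allowed for.

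The section does not say which comparison d = 1 refers to, whether the test is one- or two-sided, or what the allocation ratio is. The Statistical analysis section plans ANOVA for all primary and secondary outcomes and names no contrast and no pooling of arms. The Abstract and Background give the main objective as the programme against waiting list, and make guided versus unguided delivery a secondary, exploratory objective. The Discussion also lists as an aim the efficacy of the fully self-applied format.

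**The concern.** A reader who meets a three-arm design, a standardised mean difference and an ANOVA will apply the 80% to one of two things: each active arm against waiting list, or the three-group test. Neither has it at 57.

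This matters most for the self-applied arm, whose efficacy is an aim in its own right. If that arm does not differ significantly from waiting list, the result will be read as having a 20% chance of missing d = 1, when the chance is about 30%. The choice between a pooled and a per-arm test also needs to be fixed before data are seen, because the Statistical analysis section leaves the method open to revision before analysis.

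**Working it through.** **Inputs from the article.** N = 57, three arms, d = 1, power 0.80, alpha 0.05, dropout 30%.

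**Assumptions, not in the article.** 1:1:1 allocation, equal loss in all arms, information from completers only, no baseline adjustment.

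**Completers.** 57 / 3 = 19 per arm; 57 × 0.70 = 39.9, or 13.3 per arm. Both 13 and 13.3 are carried through.

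**Reproducing 57.** Two routes give it exactly with the correct division by 0.70.
- Both programme arms pooled against waiting list (2:1), two-sided t test: 24 v 12 gives 0.785 and 26 v 13 gives 0.818, so 13 per arm are needed. 13 / 0.70 = 18.6, rounded up to 19; 19 × 3 = 57.
- One arm against waiting list, one-sided 5%, normal approximation: n = 2(1.645 + 0.842)² / 1² = 12.4, rounded up to 13; again 19 per arm and 57 in total. With the exact t distribution this route needs 14 completers, hence 20 per arm and 60.

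**Two-sided per-arm test does not give 57.** The exact t test needs 17 completers per arm; 17 / 0.70 = 24.3, rounded up to 25; 25 × 3 = 75. The normal approximation gives 16, then 23, then 69.

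**Power with 57 randomised and 30% lost.** For two groups the noncentrality is d / √(1/n₁ + 1/n₂), referred to a noncentral t with n₁ + n₂ − 2 degrees of freedom.
- Per arm, two-sided, 13 v 13: 1 / √(2/13) = 2.55, critical value 2.06 on 24 df, power 0.687. At 13.3 per arm, 0.697.
- Per arm, one-sided: 0.797 and 0.806.
- Pooled, two-sided, 26 v 13: 1 / √(1/26 + 1/13) = 2.94, critical value 2.03 on 37 df, power 0.818. At 26.6 v 13.3, 0.827.

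For the three-group omnibus F, the noncentrality is 3n·f², where f is the SD of the group means in units of the within-group SD.

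| Reading of d = 1 | f | 3n·f² at n = 13 | Power, 13 / 13.3 per arm |
|---|---|---|---|
| Means 0, 0.5, 1 | √(1/6) = 0.408 | 6.50 | 0.58 / 0.59 |
| Means 0, 1, 1 | √(2/9) = 0.471 | 8.67 | 0.72 / 0.73 |
| f set to d/2 | 0.500 | 9.75 | 0.77 / 0.78 |

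**Detectable effect.** Solving the two-sided per-arm test for 80% power gives d = 1.15 at 13 per arm and 1.13 at 13.3. With no dropout (19 per arm) its power at d = 1 would be 0.851, so the shortfall arises once the 30% loss is applied.

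**The case against.** The strongest reply is that 57 is right. The main objective is the programme against waiting list, and comparing the two formats is only exploratory. On that reading the natural primary test pools the two active arms. It reproduces 57 with the dropout division done correctly and has a little over 80% power. This stands, and it rules out a stronger inference that a reader might draw, namely that no reading of 57 gives 80% or that the authors made an arithmetic slip in allowing for dropout. The documents show no such slip. What remains is that no section says the arms are pooled, that the test is one-sided, or that any contrast replaces the three-group ANOVA.

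A second reply is that baseline scores are collected and could be adjusted for. At an assumed baseline–outcome correlation of 0.5, per-arm power at 13 completers rises to 0.81; at 0.4 it is 0.76. The article states neither the adjustment nor a correlation, so this cannot support the stated figure. Nor can multiple imputation, which is planned but does not by itself restore the information lost to dropout.

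A third reply is that a condensed article may leave contrast and sidedness to a fuller document. That is fair as far as the silence goes. But the article does state both a power and an analysis, and the two do not match as written.

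A reader might also infer that the Background undercuts d = 1, since it reports that "the results so far indicate a small but significant effect size of these self-help interventions compared to a control condition". That sentence concerns self-help over the Internet in general and gives no figure. The sample-size section rests d = 1 on a similar study, described in the Background as a computer-assisted flying-phobia programme, and on reviews that cannot be checked here. The article does not support calling d = 1 wrong.

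**Conclusion.** The concern holds in conditional form. With 57 randomised and 30% lost, two-sided power at d = 1 is about 0.69 to 0.70 for each NO-FEAR Airlines arm against waiting list. It is 0.58 to 0.78 for the omnibus ANOVA, the only kind of analysis the article plans for the primary outcomes. The stated 0.80 holds for the pooled two-sided contrast (0.82 to 0.83) or approximately for a one-sided per-arm test, neither of which is named. These figures rest on equal allocation, equal loss, completer-level information and no baseline adjustment; the article fixes none of these except the overall 30% loss. The defect is a power claim not tied to the test that delivers it, rather than a sample size that is wrong on every reading.

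**What to change.** Keep N at 57 and amend the sample-size and analysis sections together:
- Prespecify the two-sided contrast of both NO-FEAR Airlines arms pooled against waiting list as the primary test. It matches the stated main objective. Give its power as about 0.82 at d = 1 with 30% loss.
- State that each arm against waiting list has about 0.70 power at d = 1, with a detectable d of about 1.13 to 1.15 at 80% power.
- Label the per-arm and guided-versus-unguided comparisons as secondary.
- State the allocation ratio and the sidedness.

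No extra participants are needed. The cost is some rewording and a less favourable stated power for the per-arm tests. If 80% two-sided power for each arm is wanted instead, the same assumptions call for about 75 randomised (69 by the normal approximation).

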### Ethics

This trial received approval from the Ethics Committee of Universitat Jaume I (Castellón, Spain) (20 December 2014) and will be conducted in compliance with the study protocol, the Declaration of Helsinki, and good clinical practice. Data security/confidentially will be guaranteed; all relevant EU and Spanish legislation on privacy will be observed and respected. Access to the Internet platform is through a unique username-password combination, and all transferred data will be secured following the AES (*Advanced Encryption Standard*) polynomial m(x) = ×8 + ×4 + ×3 + × + 1. The consent form will be explained and required from all participants. Important protocol modifications will be communicated to relevant parties (i.e., trial participants, trial registries, journals, ethical committee and researchers).

### Eligibility criteria

The study sample will consist of adults from 18 years old who meet the Diagnostic and Statistical manual for Mental Health Disorders-Version 5 (DSM-5) (APA, 2013) criteria for specific, situational phobia (FP). They are required to have adequate knowledge to understand and read Spanish, access to the Internet, and the ability to use a computer. Exclusion criteria for the study are as follows: a) receiving psychological treatment for FP; b) diagnosis of a severe mental disorder: abuse or dependence on alcohol or other substances, psychotic disorder, dementia or bipolar disorder; c) presence of depressive symptomatology, suicidal ideation or plan; d) Presence of heart disease; e) Pregnant women (from the fourth month). Receiving pharmacological treatment is not an exclusion criterion during the study period, but any increase and/or change in the medication during the study period will imply the participant’s exclusion from subsequent analyses. A decrease in pharmacological treatment is accepted.

Participants with comorbid and related disorders (i.e., panic disorder, agoraphobia, claustrophobia or acrophobia) will be included when FP is the primary diagnosis. Participants who do not meet the inclusion criteria will be encouraged to seek treatment alternatives better suited to their specific needs.

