## Background

Flying Phobia (FP) is a common and disabling disorder classified as a situational specific phobia [1]. The symptoms of FP can encompass several diagnostic categories (such as panic disorder, agoraphobia, claustrophobia, or acrophobia), making diagnosis and treatment complex [2, 3]. Recent studies have established a lifetime prevalence of approximately 2.5 % of the adult population [4], although previous epidemiological studies reported prevalence estimates ranging from 10 to 40 % [5, 6]. Moreover, research has pointed out that around 25 % of the adult population suffers from anxiety when taking a flight, about 10 % avoid flying due to the intensity of their fear, and approximately 20 % depend on alcohol or anxiolytics to fly [7].

Consequences of FP are far-reaching, resulting in substantial social costs from the patient’s perspective, which for some authors are incalculable [8], as well as the costs for aeronautical companies [9, 10]. Interference caused by this problem is diverse and varies depending on personal demands or needs, as well as patients’ geographical location. According to Busscher et al. [2], 7 % of the population experience serious interference in daily life and social functioning due to FP. Personal consequences of suffering from FP may consist of limited professional opportunities or leisure options and changing or disrupted relationships, and it often causes shame and emotional distress when the person faces the thought of flying [4, 11, 12].

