### Recruitment, randomization and blinding

The study will be advertised online via professional websites (i.e., LinkedIn), non- professional social-networks (i.e., Facebook and twitter), and advertisements in newspapers. Furthermore, posters will be placed in local universities (Universitat Jaume I and Universitat de València) and travel agencies. People who are interested will be directed to the research website (www.fobiavolar.es), where they will find further information about the study and what participation entails, as well as an informed consent form. Individuals can request participation through the website and by signing the informed consent form. After website registration, the clinical team will contact participants by telephone to screen for the inclusion and exclusion criteria and explain the research terms (i.e., study design, treatment length, or treatment rationale). Participants who meet the criteria will be administered a diagnostic telephone interview at the time of the screening, or another time will be arranged. Then, participants will be randomly assigned to one of the three experimental groups. The allocation schedule will be generated through a computer randomization program (Epidat 4.0) by an independent researcher who will be unaware of the characteristics of the study. The allocation schedule will be communicated to the study researchers via phone call. Patients will agree to participate before the random allocation and without knowing to which treatment they will be assigned. However, for practical reasons, participants and researchers will not be blind to the treatment conditions. Participants will be free at any time to withdraw from the treatment or the study without giving any explanation.

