### Statistical analysis

Intention-to-treat (ITT) and per protocol analyses (PPA) will be conducted following the CONSORT recommendations and SPIRIT guidelines for reporting the results [48–50]. Differences in demographic and baseline clinical characteristics will be computed using Chi-square tests for categorical variables and analysis of variance (ANOVA) for continuous data. ANOVA will be conducted to explore the effects of the treatments on all primary and secondary outcomes. Analyses of post-treatment flights will be carried out using Chi-square tests to evaluate group differences, including the number of flights taken and number of safety behaviours performed. Moreover, effect sizes and confidence intervals of the mean will be conducted, following the author’s recommendations and recent literature [66, 67]. Assuming that missing data will be missing at random, it will be handled using multiple imputations (MI) [68]. All analyses will be conducted using IBM SPSS statistics for Windows, version 22.

In any case, the state of the art of analytic methodology for RCT will be reviewed before analyzing the data, in order to apply the most appropriate statistical analysis procedure.

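### As worded, the medication rule removes randomised participants from every analysis, including the ITT analysis the protocol commits to

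*Protocol article*

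**What the plan says.** Eligibility criteria allows medicated people into the trial: "Receiving pharmacological treatment is not an exclusion criterion during the study period". It then adds that "any increase and/or change in the medication during the study period will imply the participant’s exclusion from subsequent analyses", and closes with "A decrease in pharmacological treatment is accepted".

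Statistical analysis names two analysis sets: "Intention-to-treat (ITT) and per protocol analyses (PPA) will be conducted following the CONSORT recommendations". Missing data are to be handled by multiple imputation under a missing-at-random assumption. That section does not mention medication, and nothing elsewhere in the article says which of the two sets the medication rule governs.

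Three other statements bear on the point. Recruitment, randomization and blinding says that "participants and researchers will not be blind to the treatment conditions". Study design has waiting-list controls randomised to one of the two treatments after six weeks. Instruments schedules assessments at baseline, post-treatment, 3 months and 12 months.

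**The concern.** An ITT analysis keeps every randomised participant in the arm to which they were allocated, whatever happens later. A rule that removes people from the analyses because of something during the study cannot also apply to that set. The eligibility text places no limit on which analyses it means, so an analyst who follows it literally cannot deliver the ITT analysis.

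The choice of event matters too. The rule removes participants whose medication rises or changes and retains those whose medication falls. If a rise tends to go with persisting or worse fear, the rule takes out poorer outcomes and leaves better ones. If rises are also more frequent in one arm, the arms are no longer comparable as randomised. At stake is who enters the main comparison, and whether that comparison still has the protection of randomisation.

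**Working it through.** **1. Is there a figure in the plan to reproduce?** Not on this point. The article gives no expected rate of medication change and no size for either analysis set. The minimum sample of 57 is used below only to turn percentages into people.

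**2. The two sections side by side.**
- Eligibility criteria: the trigger is a medication increase or change, the period is the study period, and the consequence is that the participant is excluded from later analyses. No set is named.
- Statistical analysis: both ITT and per-protocol analyses are promised, with no exception for medication.
- If the rule covers both sets, the ITT promise fails. If it covers the per-protocol set only, the two sections agree, but no sentence says so.

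**3. How long the rule can act.**
- Treatment versus waiting list: controls are moved to a treatment after 6 weeks, and the treatment period is at most six weeks. The exposure is about six weeks.
- Guided versus unguided: follow-up runs to 12 months, so the exposure is up to 12 months.

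**4. Is the event plausibly related to outcome and arm?** This step is inference. The Background reports that "approximately 20 % depend on alcohol or anxiolytics to fly", which ties anxiolytic use to the disorder. The Intervention section encourages every patient to take a real flight after the program, an occasion on which medication use could rise. Controls wait untreated while the active arms work through anxiety-provoking scenarios, so reasons for a change may differ by arm. Allocation is known to those who would judge whether a change has occurred.

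**5. Illustrative size.** Assumptions, none from the documents: the outcome is normal with SD 1; a fraction p of one arm is removed; the other arm loses nobody.
- Upper bound, where those removed are exactly the worst scorers: shift in the arm's mean = φ(z) / (1 − p), where z is the (1 − p) quantile of the standard normal and φ its density.
- p = 0.10: z = 1.282, φ = 0.1755, shift = 0.1755 / 0.90 = 0.195
- p = 0.15: z = 1.036, φ = 0.2332, shift = 0.2332 / 0.85 = 0.274
- p = 0.20: z = 0.842, φ = 0.2800, shift = 0.2800 / 0.80 = 0.350
- If removal is driven by a variable correlated r with the outcome, multiply by r. At r = 0.5 the shifts are about 0.10, 0.14 and 0.175 SD.

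With equal allocation (the ratio is not stated) 57 / 3 = 19 per arm, so these fractions are 1.9, 2.85 and 3.8 people, or roughly two, three and four.

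**6. Direction.** Removing the worst scorers from the waiting list flatters the control and understates the effect. Removing them from an active arm flatters treatment and overstates it. Equal removal in both arms would largely cancel in the difference.

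**The case against.** The best defence is that a stable-medication rule is a familiar per-protocol criterion, that the article defines neither set, and that set definitions are often left to a fuller document. On that reading there is ambiguity and no contradiction. A related reading is that only data after the medication change are dropped, with imputation filling the gap. Both are possible intentions. However, the sentence speaks of excluding the participant, names no set, and is not linked to imputation. This is a stated rule and not a detail left out. On the second reading, discarding scores because medication rose would also strain the missing-at-random assumption.

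Other parts of the defence stand, and they limit the point. A reader might infer more than the article supports in five ways:
- That the waiting-list comparison is exposed for 12 months. It is not, because controls receive treatment after six weeks.
- That medication increases are known to result from fear or allocation. The article does not say this. Its 20% figure concerns alcohol or anxiolytics used to fly and is not a rate of medication change in this trial. The eligibility text refers to pharmacological treatment in general.
- That the bias favours treatment. No net direction can be established.
- That lost power is part of the case. With one person fewer than 13 per arm, two-sided power at d = 1 goes from 0.69 to 0.65. On a one-sided normal basis that reproduces 57, power goes from 0.83 to 0.79 at 10% exclusion. The low starting value reflects the unstated sidedness of the sample size calculation, which is a separate matter.
- That the words on change and decrease form a second contradiction. A decrease is literally a change, but the next sentence reads naturally as an exception. This is a wording repair.

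**Conclusion.** The rule is wrong as written. It excludes participants from analyses without limitation, for an event that can follow randomisation, in a plan that commits to ITT. That conclusion rests on the text alone and needs no assumption about rates.

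The possible bias rests on inference: that medication increases go with worse fear and may differ by arm. Under assumed one-arm exclusions of 10% to 20%, it is at most 0.20 to 0.35 SD, and about half that at an assumed correlation of 0.5, with either sign. Against the planned d = 1, the upper bound is 20% to 35% of the effect. The article states no separate expected difference for guided versus unguided delivery, where the window is longest and a shift of this size could matter more.

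**What to change.** Amend the eligibility text and add one sentence to Statistical analysis, to this effect: participants whose medication increases or changes after randomisation continue their scheduled assessments and remain in the ITT analysis in their allocated arm; the medication rule defines exclusion from the per-protocol set only; the number of such participants is reported by arm. State explicitly that the accepted decrease is an exception to the word change.

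The sample size is unaffected. The cost is protocol wording, continued assessment of these participants on the existing schedule to 12 months, and a record of medication changes. The article does not say whether assessment continues after exclusion, so that commitment has to be added. Table 1 lists no medication measure, but the present rule already cannot be applied without recording changes. No position is taken on which medication rule is clinically right; the two sections need to be reconciled on who is analysed.
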